## Abstract

**Background:**

Post dural punction headache (PDPH) occurs in 10% to 40% of the patients who had a lumbar puncture. Its symptoms can be severe and incapacitating. The epidural blood patch is widely accepted as the treatment of choice for postdural puncture headache. Uncontrolled studies report rapid recovery after patching in 90% to 100% of treated patients. However, sufficient evidence from randomised, controlled clinical trials is lacking.

**Methods:**

BLOPP (blood patch for post dural puncture headache) is a randomised, single centre, observer-blind clinical trial. Patients with PDPH for at least 24 hours and at most 7 days after lumbar puncture will be randomised to treatment with an epidural blood patch (EDBP) or to conventional treatment, i.e. 24 hours bed rest and ample fluid intake. PDPH 24 hours after treatment, classified on a 4-point scale (no, mild, moderate, severe) is the primary outcome. The secondary outcome is the presence of PDPH 7 days after treatment. We estimated that a sample size of 2 × 20 patients would provide us with a power of 80% to detect a relative reduction in number of patients with persisting PDPH after 24 hours of 50% at the usual significance level α = 5%, taking into account that in approximately 10% of the patients the PDPH will have resolved spontaneously after one day.

**Discussion:**

The EDBP is accepted as the treatment of choice for PDPH although randomised, controlled data is scarce. Our randomised, observer-blind clinical trial enables us to compare the efficacy of two clinically practiced methods of PDPH treatment; EDBP versus conventional treatment, as they are applied in clinical practise.

## Background

Headache complicates approximately 10 to 40% of dural punctures [1]. This postdural puncture headache (PDPH) is typically orthostatic; provoked or aggravated by a vertical or upright position and relieved by a horizontal position. PDPH is probably caused by cerebral spinal fluid leakage through the dural rent, into the epidural space. The leakage causes a decrease in CSF pressure and volume, leading to traction on pain-sensitive structures in an upright position. Besides of headache, the patient may complain of diplopia, tinnitus, dizziness, and myalgia. PDPH may occur immediately after spinal tap, but it starts within 48 hours after the procedure in more than 90% of the patients. PDPH and accompanying symptoms are self-limiting. They generally resolve within 7 days or less, in 80% of the cases. In a small minority of cases, the symptoms may persist for weeks or even months [2]. During an episode of PDPH the patient may be completely incapacitated and confined to bed. Obviously this has financial, social and psychological repercussions.

Different prophylactic measures such as: small needle size, the use of Sprotte's needle, reinsertion of the stylet before withdrawing the needle, and direction of the brevel perpendicular to the dura, have all been shown to reduce the occurrence of PDPH [3-6]. If, despite the prophylactic measures, PDPH occurs, epidural blood patch (EDBP) may be a beneficial therapeutic intervention. EDBP has gained popularity as a therapeutic measure for PDPH. It involves the injection of 10–20 ml of autologous blood into the epidural space around the site of the spinal tap. Gormly introduced this technique in the 1960's [1]. He noticed that inadvertent bloody spinal taps were less often complicated by PDPH. He theorised that the epidural bleeding might lead to clot formation over the dural rent, preventing CSF leakage into the epidural space. He therefore continued to treat 6 subjects suffering from PDPH with EDBP, locating the epidural space with the hanging-drop or loss of resistance method. All 6 subjects were relieved of their complaints.

Many observational studies followed; they reported success rates of the EDBP for PDPH between 70% and 90% [7-12]. Seven controlled trials concerning prophylactic treatment have been published [13-19]. One of these studies was not blinded [18], three were not randomised [14-16], one was only reported as an abstract [17]. One other study [13] compared prophylactic EDBP versus no blood patch among obstetric patients and reported a high success rate. In this study adverse effects were not mentioned, which prevents firm conclusions. The latest study [19], in which prophylactic EDBP was compared to a sham procedure in a double blind setting, showed no decrease in the incidence of PDPH between the two groups. The effectiveness of prophylactic treatment does not seem to have been established firmly.

Only one randomised and blinded trial concerning the therapeutic effect of EDBP has been reported [20]. In this study 12 patients, suffering from PDPH for more than 4 days, despite conservative treatment following lumbar puncture, spinal anaesthesia or myelography, were randomly allocated to EDBP or sham treatment. In the placebo group none of the patients noted complete relief of pain. In the treatment group 5 of the 6 patients obtained immediate relief. Subsequently placebo group patients were also treated with an EDBP, resulting in complete relief of PDPH in all patients. The size of the study, the crossover effect, and the absence of any documentation regarding the effectiveness of blinding of the observers and patients, makes it difficult to draw firm conclusions from this study.

A Cochrane review on prophylactic and therapeutic blood patching [21] argued that further randomised trials of epidural blood patching must be carried out before the balance of risks and benefits of this intervention can be properly assessed".

Therefore, we decided to conduct a randomised, controlled, clinical trial comparing the efficacy of the EDBP with conservative treatment, consisting of 24 hours of bed rest and adequate fluid intake for the treatment of PDPH.

## Methods

### Inclusion criteria

To be included in the study, patients should have PDPH longer than 24 hours and not longer than 7 days after a diagnostic spinal tap. Furthermore patients should be aged 18 years or older. Written informed consent is required.

### Exclusion criteria

Excluded are patients with relative contra-indications for lumbar puncture: hemorrhagic diathesis and space-occupying intracranial lesions, and patients with a body temperature over 38° Celsius.

### Design

This is an observer-blind prospective, controlled and randomised parallel group study.

### Active treatment

Patients allocated to active treatment will receive an EDBP on the day of randomisation. The subject is placed in the lateral position, after which the back is flexed, sterilised and draped. Sterile gloves are used. A needle (Spinocan canule: 0.9 × 88 mm/206 × 3.5) is placed in the epidural space, using the loss of resistance technique. Subsequently, 20 cc of blood is than drawn from the antecubital vein, and injected slowly into the epidural space, after which the needle is removed. The subject is held in the supine position for a few minutes, after which there are no further restrictions.

### Control treatment

Conservative treatment consists of the advice to take 24 hours bed rest and drink at least 2.0 litres of fluid a day. The use of painkillers is not prohibited. Treatment with EDBP is not an option during the study period of 7 days, not even when conservative treatment fails.

### Outcomes

The primary outcome is whether or not headache is present at 24 hours after the start of treatment. Headache is classified on a 4-point scale (no, mild, moderate, severe). *Mild headache *is defined as: postural headache slightly restricting daily activities. The patient is not confined to bed and there are no associated symptoms. *Moderate headache: *postural headache confining the patient to bed for part of the day. Associated symptoms are not necessarily present. *Severe headache: *postural headache where the patient is bedridden for the entire day and associated symptoms are always present. The associated symptoms are: nausea, vomiting, dizziness, hearing loss, hyperacusis, tinitus, photophobia, diplopia, stiffness of the neck and scapular pain [2].

Secondary outcome measures are the presence of headache at day seven after the start of treatment, and the number of days until headache subsides.

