### Follow-up and blinding

The follow-up visits are carried out by telephone, by a research nurse at the trial office, 24 hours after randomisation, and at 1 week after randomisation. The research nurse is kept blind to the treatment allocation. At the beginning of the telephone interview the patients are instructed not to inform the observer of the treatment they received. The effectiveness of the blinding will be checked in a sample of 12 patients, by letting the research nurse fill in a forced choice item indicating the treatment allocation.

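### The 24-hour severity grades rest on confinement to bed, which is also the control treatment, so the scale can hint at the arm to the blinded nurse and mixes severity with treatment.

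*Protocol article*

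**What the plan says.** All places are in the Methods of the protocol article.

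- **Outcomes**, the primary outcome: "The primary outcome is whether or not headache is present at 24 hours after the start of treatment". Headache is also classified as none, mild, moderate or severe.
- **Outcomes**, the grades. Mild: "The patient is not confined to bed and there are no associated symptoms". Moderate: "postural headache confining the patient to bed for part of the day". Severe: "postural headache where the patient is bedridden for the entire day and associated symptoms are always present".
- **Control treatment**: "Conservative treatment consists of the advice to take 24 hours bed rest and drink at least 2.0 litres of fluid a day".
- **Active treatment**, after the injection: "The subject is held in the supine position for a few minutes, after which there are no further restrictions".
- **Follow-up and blinding**: a research nurse who does not know the allocation telephones 24 hours and one week after randomisation. The safeguard during the call is this: "At the beginning of the telephone interview the patients are instructed not to inform the observer of the treatment they received". A forced-choice guess of the arm is to be collected in 12 patients.
- **Statistical analysis**: the numbers with headache at 24 hours are compared between arms. No analysis of the severity grades is named.

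The Discussion says that patients know their treatment, so the nurse is the only blinded party.

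**The concern.** The feature that separates mild from moderate from severe is time spent in bed. The behaviour that separates the control regimen from the patch regimen over the first 24 hours is also time spent in bed. The nurse rates patients just as that period ends.

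Two things follow. First, anyone applying the scale as worded learns something about bed status, and so something about the arm. The instruction to patients covers naming the treatment; it does not cover a truthful answer about having been in bed. Second, the grade itself is distorted. A control with a slight headache who followed the advice was in bed, and so fails the literal definition of mild. A patched patient with the same headache meets it.

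At stake are the value of the trial's only blinding and the comparability of the severity grade between arms. The primary yes/no outcome is at risk only at one remove.

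**Working it through.** **1. Inputs from the plan.** 20 patients per arm; 10% spontaneous resolution at 24 hours, so 90% of controls still have headache; relative reductions of 50% and 80%.

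- Patched patients still with headache: 0.90 × 0.50 = 0.45, or 0.90 × 0.20 = 0.18.
- The stated sample size reproduces. For 90% v 45%, two-sided 5% (sidedness assumed) and 80% power, the uncorrected n is [1.96·√(2 × 0.675 × 0.325) + 0.8416·√(0.09 + 0.2475)]² / 0.45² = 15.8. With continuity correction, (15.8/4)·[1 + √(1 + 4/(15.8 × 0.45))]² = 20.0 per arm. The 45% and 18% are therefore fair readings of the plan's alternatives.

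**2. The overlap, side by side.**

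| Grade | Bed criterion | Control following the advice | Patched patient |
|---|---|---|---|
| None | none stated | in bed on advice | no restriction |
| Mild | not confined | criterion not strictly met | can be met |
| Moderate | part of the day | headache or advice? | headache |
| Severe | entire day, with associated symptoms | headache or advice? | headache |

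The bed criterion does not separate *none* from *mild*, which is the boundary that decides the primary outcome. It acts on the three grades above.

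**3. Size of the cue.** Let c be the share of controls in bed and b the share of patched patients in bed. With 1:1 allocation, a nurse who guesses control when the patient was in bed, and patch otherwise, is right with probability (c + 1 − b)/2. The documents give neither c nor b, so both are assumptions. The upper values of b equal the shares still with headache in step 1.

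| c | b | Correct guesses |
|---|---|---|
| 0.50 | 0.45 | 52.5% |
| 0.50 | 0.18 | 66% |
| 0.80 | 0.45 | 67.5% |
| 0.80 | 0.18 | 81% |
| 1.00 | 0.45 | 77.5% |
| 1.00 | 0.18 | 91% |

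Chance is 50%. The cue runs from almost nothing to strong, and in no row is it certain.

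**4. Would the planned check detect it?** With 12 forced choices, at least 10 correct are needed to beat chance at one-sided 5% (10 or more: p = 0.019; 9 or more: p = 0.073). The probability of reaching 10 is 25% if the true rate of correct guesses is 70%, 56% at 80% and 89% at 90%. The check could easily miss a moderate leak, and in any case it measures a leak without preventing one.

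**5. What a shaded rating could do (illustration only).** Each re-rated patient moves an arm by 1/20 = 5 percentage points. Two-sided Fisher exact tests:

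- 18/20 v 13/20: p = 0.127; v 12/20: p = 0.065; v 11/20: p = 0.031. Here two re-ratings cross 5%.
- At the plan's 50% reduction, 18/20 v 9/20 gives p = 0.006. Two re-ratings against the patch give 18/20 v 11/20, p = 0.031, still significant.
- Near the 80% reduction (about 18/20 v 4/20), two re-ratings give 18/20 v 6/20, p = 0.0002.

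The first line was chosen because it tips. Nothing in the documents says that two re-ratings would occur.

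**The case against.** A reader might infer that grading the headache reveals the arm and that the observer blinding is lost. The documents do not support this, and the case against it is good.

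- **The cue is probabilistic.** Bed rest is only advised, so some controls will not comply. Patched patients with persisting headache or back pain may be in bed too. Step 3 shows accuracy as low as about 53%. This stands.
- **The primary outcome does not need the bed question.** Outcomes and Statistical analysis make it present or absent. The Abstract does attach the 4-point scale to the primary outcome, but the bed criterion does not divide none from mild. The answer also comes from a patient who already knows the treatment, a limit that the Discussion accepts. This stands: the route to the primary result is indirect.
- **The interview is not shown.** That the nurse asks about bed, and in what order, is inferred from the scale. An article may leave the script to the full protocol, which may already ask about presence first. This stands as a caution. The grade definitions, however, are stated, and the overlap lies in them.
- **The grades already mean confinement by headache.** That is the natural reading of moderate. It does not rescue mild, which simply requires no confinement, and severe is worded loosely. If the nurse has to ask why the patient was in bed, the honest reply may disclose the arm.
- **The one-week call.** A reader might extend the point to it. The advised rest is long over by then, so there is no direct cue; only a guess remembered by the same nurse could carry over. That is speculation and no part of this point.

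**Conclusion.** The point holds in a limited form. As worded, the severity scale overlaps with the control treatment in the same 24 hours. It confounds the severity grade with the arm and gives the only blinded party a partial, possibly strong, cue.

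The size of the cue rests on assumed shares in bed: about 53% correct guesses at 50% of controls v 45% of patched patients, and 68–91% at 80–100% v 18–45%. The effect on the primary outcome is indirect. It needs a nurse who has inferred the arm and who shades a borderline yes/no answer, and its size cannot be derived from the documents. The Fisher figures show only how few ratings matter with 20 per arm when a result is already close. The change is worth making because it is cheap, not because bias in the primary result has been shown.

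**What to change.** For the 24-hour call:

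1. Ask first whether headache is present, and record and lock yes/no before any question on bed or activity.
2. Define all three grades by restriction or confinement that the headache causes, and state that rest taken on advice does not count.
3. Ask the bed items last, without asking whether rest was advised.

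If the interview script already does this, the article's grade definitions need only be brought into line with it. The treatments are untouched.

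The cost is a revised script and data form, with no extra staff or visits. The downside is that the trial is already under way, so severity in completed calls was graded under the old wording. Those grades should be flagged and shown separately from later ones.

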### Treatment complications

A systematic assessment of complications of EDBP will be carried out. Back pain will be assessed systematically, and classified as no, mild moderate, severe.

### Statistical analysis

The number of patients with headache at 24 hours after start of treatment will be compared between the two treatment strategies. The effect of treatment on the occurrence of the headache will be expressed as an odds ratio with 95% confidence interval. Adjustment for the effect of potential confounders, such as age and sex, will be made by multiple logistic regression analysis. The number of days until headache relief will be compared with Kaplan-Meier survival analysis techniques; observations will be censored at the end of the study period, i.e. 7 days. Adjustments for the effect of potential confounders will be made with proportional hazards regression [22].

### Sample size

A trial with 20 patients in each treatment group will provide us with a power (1-β) of 80% to detect a relative reduction in number of patients with persisting PDPH after 24 hours of 50% (OR = 12) and a power of 99% to detect a relative risk reduction of 80%, (OR = 81, at the usual significance level α = 5%, taking into account that in approximately 10% of the patients the PDPH will have resolved spontaneously after one day.

### Recruitment of eligible patients

Patients receiving a diagnostic dural puncture are informed about the possibility of developing PDPH. They all receive written information about the study. A subject suffering from headache after a dural puncture will be advised to contact his physician. The physician evaluates whether the headache is a PDPH or not. When the conclusion is that the subject is suffering from PDPH, he or she is asked to participate. Randomisation is done by a telephone call, by the investigator.

### Randomisation procedure

The randomisation procedure is carried out by one of the investigators (RO or [name]). During the telephone contact, while the patient is entered into the computer database the treatment allocation (based on a random number generator) is provided by the computer. The patient cannot be entered twice into the study, nor can the entry be erased.

### Ethical considerations and informed consent

The local medical ethics committee and review board approved this study. Written informed consent will be obtained from all patients, by asking them to return the form by mail or in person, after the randomisation by telephone.

### Baseline data

At baseline, patient demographics age and gender will be registered. Both have been proven to be independent risk factors for the development of PDPH. Clinical characteristics, such as headache characteristics, other complaints, and use of analgesics will be noted. Information concerning needle type, size and re-insertment of the stylet before withdrawing is registered, since all three factors are independent risk factors for the development of PDPH [3-5]. Furthermore the severity of the PDPH is registered on a four-point scale.

### Follow-up and blinding

The follow-up visits are carried out by telephone, by a research nurse at the trial office, 24 hours after randomisation, and at 1 week after randomisation. The research nurse is kept blind to the treatment allocation. At the beginning of the telephone interview the patients are instructed not to inform the observer of the treatment they received. The effectiveness of the blinding will be checked in a sample of 12 patients, by letting the research nurse fill in a forced choice item indicating the treatment allocation.

## Discussion

The EDBP, is widely accepted as the treatment of choice for PDPH. In a review of the literature on this subject however, we found only little evidence to justify its use in general practice [21]. Therefore, we decided to conduct an observer blinded, randomised, controlled, study comparing the therapeutic efficacy of the EDBP to the efficacy of conservative treatment.

Our study design not only enables us measure the effectiveness of the EDBP, but also its efficiency. The number of days spent with headache after treatment in the two groups will be characterised as incapacitated-days. Immediate relief of headache, and reduction of the number of incapacitated-days is the ultimate goal of this treatment. By taking into account the adverse effects of EBPD, most notably lower back pain, we will be able to make a more realistic estimate of the overall effect of EPBD.

The observer-blind method we have chosen enables us to compare the two treatment strategies of interest as if they are carried out in normal practise, without the artificial circumstances created by sham treatment, in futile attempts to maintain patient blinding. So a genuine comparison is made between the experimental treatment and normal clinical practise. Because patients are of course aware of the nature of the treatment, the study design limits our ability to assess the placebo effect of the epidural blood patch. One may argue that this may lead to overestimation of the effect of the blood patch. We think that for a treatment of a self/limiting condition this is not really a drawback. Another potential limitation is the small sample size of our study. Although our trial will turn out to be the largest randomised study of therapeutic EDBP ever, a sample size of 20 patients in each treatment group will provide us sufficient power (1-β = 80%) to detect a relative reduction in the risk of PDPH after 24 hours of 50%. Much depends therefore on our assumption that only in approximately 10% of the patients the PDPH will have resolved spontaneously after one day. Currently, the study is well underway, and we expect to be able to report its results in the end of 2005.

## Conclusion

EDBP is accepted as the treatment of choice for PDPH although randomised, controlled data is scarce. Our randomised, observer-blind clinical trial enables us to compare the efficacy of two clinically practiced methods of PDPH treatment; EDBP versus conventional treatment, as they are applied in clinical practise.

## List of abbreviations

CSF: Cerebrospinal fluid

EDBP: Epidural blood patch

PDPH: Post dural punction headache
